#### Long-term (follow-up) endpoints

Occurrence of depression within 36 months (dichotomous)
Admission to psychiatry with depression as the primary diagnosis (dichotomous)New start of antidepressant treatment after baseline (dichotomous)Clinically relevant changes in HADS score over 36 months (categorical)Changes in status from HAM-D score from baseline over 36 months (categorical, change in category 13–17, 18–24, and 25–52 points)Number of days during antidepressant treatment from baseline over 36 months (continuous)Changes in FEV_1_ from baseline over 36 months (continuous)

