## Methods

### Design

This is a randomized open-label, superiority, multicenter, 2-arm intervention study, in which it is examined if a “high-intensity” intervention causes fewer people (diagnosed with COPD) to smoke after 12 months than in a “low-intensity” intervention in people diagnosed with COPD. The effect on survival for 12, 24, and 48 months; incidence of COPD exacerbations; number of admissions for all causes; and cardiovascular admissions will also be analyzed at the same time.

Additionally, a few sub-studies will be conducted:
Sub-study 1: We will examine the prevalence of depression/anxiety within 36 months in the “high-intensity” and “low-intensity” groups by means of questionnaires, by hospital admissions, and by recording the prescription of drugs for depression and anxiety.Sub-study 2: In a subset of patients who quit smoking from the “high-intensity” group (*n* = 50) and patients who do not quit smoking from the “low-intensity” group (*n* = 50), we are going to examine the potential changes in the respiratory microbiome within 6 months of smoking cessation attempt.

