### Data collection

The primary daily project management is handled by the project manager. In addition, a project group (investigators), consisting of health professionals from the departments involved, is trained to assist the project manager with the recruitment, sampling, and follow-up of participants. Recruitment in general practice is done by the project-trained nurse. Assignments for project staff after patient allocation are detailed in standard operating procedures (SOPs), depending on the allocation to intervention or control group.

Upon entering the program and all visits in the future (after 1, 3, 6, 12, 24, and 36 months), the participant is summoned to a conversation with staff, asking if the participant smokes (yes vs. no), and if yes, how much. In addition, a urine sample is taken with cotinine analysis for biochemical verification of smoking status and standard blood samples to examine health status at these visits (analyzed on the Department of Clinical Biochemistry, KBA). In addition, questionnaires (CAT, MRC, and HADS) are completed with the participant.

In the case of inclusion and follow-up visits after 3, 6, 12, 24, and 36 months, lung function measurement is also carried out at regular intervals by spirometry. Smoking anamnesis and height measurement are done by inclusion in the study along with weight measurement, which is only further measured after 6, 12, 24, and 36 months to monitor BMI.

The HAM-D score is measured at inclusion, and again after 12, 24, and 36 months, and if the score becomes high (≥ 25), i.e., that there is a high risk of developing depression, the participant will be advised to see their GP for further evaluation.

In addition, sputum samples are induced for microbiome analysis at the time of inclusion into the study, and again after 12 months in the first 50 participants in the “high-intensity” group who quit smoking and in the first 50 participants in the “low-intensity” group who do not quit smoking.

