Confirmation of death (including the cause of death) is obtained from the Cause of Death Register (DAR). Admissions, hospitalization, and the participant’s diagnoses are retrieved from their records. Comorbidities and prescribed therapy and filled prescriptions are recorded at inclusion and on an ongoing basis during study visits. During the trial, the following are also recorded: side effects and analyses from the paraclinical tests. At the same time, it is also stated that varenicline does not cause critical interactions with other drugs (see www.interaktionsdatabasen.dk and product summary).

Collected data will be treated confidentially by the staff associated with the project. Data will be reported in electronic case report forms (eCRF) specific to each participant, which are encrypted and stored in servers protected by Danish data security authorities with double login to REDCap (with automatic range checks during data entry to prevent unrealistic data entries). In addition to the above information, the following data are recorded by inclusion: demographic data, health status, current and previous drug consumption, current and past diseases. Physical copies of CRF are kept in locked archives for the departments involved for 15 years. A Good Clinical Practice (GCP) coordinator, independent from investigators and the sponsor, will continuously monitor the trial and ensure that recruitment, data entry, etc. have been done correctly.

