### Information from patient journals

Information from the trial participants’ journals is obtained under the study to obtain study-relevant information (information to be used for the study-specific case report form or corresponding to the data to be obtained for subsequently approved additional protocols). If informed consent is obtained from the trial participants, it is permissible for the investigators to obtain this information from the patient record. Study-relevant information includes data on COPD severity, risk profile, disease development, and relevant co-morbidity to answer the hypothesis described. The informed consent also gives investigators, COP:TRIN, their representatives, and eventual monitoring authority direct access to obtain information in the participant’s journal, etc., including electronic journal, in order to see information about the participant’s health conditions, which are necessary in order to complete the research project and in monitoring purposes, including self-monitoring and quality monitoring, as these are required to be performed. No information from patient records is obtained until informed consent has been obtained from participants.

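### Antidepressant days over 36 months are captured at study visits and compared as a raw count, so the comparison is distorted if attendance or survival differs by arm

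*Protocol article*

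**What the plan says.** Two long-term endpoints in the protocol article concern antidepressants (Outcomes, Long-term (follow-up) endpoints). One is a count: "Number of days during antidepressant treatment from baseline over 36 months (continuous"). The other is yes/no: "New start of antidepressant treatment after baseline (dichotomous"). They serve Sub-study 1, which the Design section says will work with questionnaires, "by hospital admissions, and by recording the prescription of drugs for depression and anxiety".

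The Data collection section gives different kinds of data different sources:

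- Deaths: "Confirmation of death (including the cause of death) is obtained from the Cause of Death Register (DAR").
- Admissions, hospitalisations and diagnoses "are retrieved from their records".
- Prescriptions: "Comorbidities and prescribed therapy and filled prescriptions are recorded at inclusion and on an ongoing basis during study visits".
- Visit schedule: "Upon entering the program and all visits in the future (after 1, 3, 6, 12, 24, and 36 months").

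The Information from patient journals section adds: "If informed consent is obtained from the trial participants, it is permissible for the investigators to obtain this information from the patient record". That access includes the electronic journal.

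Under Analyses, all available data are analysed by intention to treat. Continuous outcomes get a t test or Mann-Whitney U test, and dichotomous outcomes Fisher's exact or chi-squared test. Timed dichotomous outcomes are also shown as Kaplan-Meier plots. Adjusted Cox models are planned. A generalized linear model is reserved for two composites of admissions or death.

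**The concern.** The scale of the day count, its data source and its test are all stated, and together they leave out how long each person was observed. After month 6 there are only three visits, at 12, 24 and 36 months. Taken as written, someone who stops attending after month 12 has no scheduled occasion on which later prescriptions would be recorded. Deaths and admissions do not have this weakness.

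Death is a separate problem that better data capture does not remove. A person who dies on day 365 can contribute at most 365 of the 1,095 days in 36 months (3 × 365).

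At stake is the reading of Sub-study 1. If one arm is better retained or survives longer, it may record more treated days and more new starts for that reason alone, and this could be taken for an effect of the intervention on depression. The yes/no comparison of new starts by Fisher or chi-squared test has the same exposure, to a smaller degree.

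**Working it through.** **The plan's own figure.** The article gives no figure for the antidepressant endpoints. Its sample size (10% vs 20%, two-sided 5%, 90% power, pooled variance) reproduces: n per arm = [1.960 × √(2 × 0.15 × 0.85) + 1.2816 × √(0.10 × 0.90 + 0.20 × 0.80)]² / 0.10² = (0.990 + 0.641)² / 0.01 ≈ 266, so 532 in total. Recruiting 600 implies an allowance for loss of 1 − 532/600 = 11.3%, not split by arm. Nothing below changes these numbers.

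**Assumptions, none from the documents.** No true effect; D = 1,095 days; a share p is on treatment throughout; a share q starts at a uniformly distributed time and continues; a share r is followed to the end; the rest are lost at a uniform time unrelated to use; days after loss count as zero.

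**Expected recorded days.**

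- Prevalent user: rD + (1 − r)D/2 = D(1 + r)/2.
- New user: rD/2 + (1 − r)D/6 = D(1/6 + r/3).
- With p = q = 0.15: mean = 0.15 × 1,095 × (2/3 + 5r/6) = 164.25 × (2/3 + 5r/6).

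This gives 232.7 days at r = 0.90, 219.0 at 0.80, 205.3 at 0.70 and 191.6 at 0.60. Relative to 90% retention, the shortfalls are 5.9%, 11.8% and 17.6%. Whenever p = q these percentages do not depend on the level of use.

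**Simulation under the same assumptions** (300 per arm, 1,000 runs, p = q = 0.15; nominal 5%):

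| Retention | Mean days | Shortfall | t test rejects | Mann-Whitney rejects | New starts | Chi-squared rejects |
|---|---|---|---|---|---|---|
| 88.7% vs 88.7% | 231.7 vs 231.1 | none | 3.6% | 4.7% | 14.3% vs 14.1% | 5.2% |
| 90% vs 80% | 232.2 vs 219.7 | 5.4% | 7.4% | 6.1% | 14.3% vs 13.5% | 5.7% |
| 90% vs 70% | 233.2 vs 205.4 | 11.9% | 14.0% | 9.7% | 14.3% vs 12.8% | 7.5% |
| 90% vs 60% | 232.5 vs 191.2 | 17.8% | 25.0% | 13.4% | 14.3% vs 12.0% | 13.2% |

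The simulation error of a 5% rate is √(0.05 × 0.95/1,000) = 0.7 percentage points. With p = q varied from 0.10 to 0.20, rejection at 90% vs 70% ranges from 10.5% to 18.2% (t test) and from 7.2% to 13.8% (Mann-Whitney).

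**If all loss fell at month 12.** Mean observed months are 36 − 24 × loss: 33.6 at 10% loss, 31.2 at 20% and 28.8 at 30%. With use constant over time, the shortfalls are 1 − 31.2/33.6 = 7.1% and 1 − 28.8/33.6 = 14.3%. Put the other way, the better-retained arm shows an excess of 7.7% (33.6/31.2) or 16.7% (33.6/28.8). This is harsher than spread loss.

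**Treated days per observed day.** In the middle scenario the two arms have 0.223 vs 0.223 at 90% vs 80% retention, 0.224 vs 0.221 at 90% vs 70%, and 0.224 vs 0.218 at 90% vs 60%. A t test on individual proportions rejects in 5.5 to 6.5% of runs. A small gap remains because new users accumulate with time, so early loss misses the period of heavier use. Complete capture therefore matters as well as the denominator.

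**If lost participants are set to missing,** the undercount disappears, and any bias depends on how loss relates to antidepressant use. The documents give no basis for a size.

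**The case against.** The strongest reply is that the article does not say what happens to a participant lost before month 36. A reader might infer that such people are scored as low users and ranked as if fully followed. Analysing all available data allows that reading but does not state it, and a rule of this kind is commonly left to the analysis plan. This stands: the undercounting figures are conditional on truncated counts.

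A reader might also infer that the high-intensity arm will be better retained and so look harmed. It does have 30 group sessions, a hotline and buddy matching. But the sessions end at day 180, scheduled calls end at week 42 unless a relapse prolongs them, and one visit schedule is given without distinction by arm. Unequal retention is plausible, not documented, and with equal loss there is no bias on these assumptions.

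Three further points have weight. Journal access is already consented, so prescriptions after a missed visit are not unobtainable; still, the sentence on prescriptions ties their recording to visits. The planned Cox model can censor new starts at last contact or death, so time-to-event analysis is not absent; it is presented as an adjusted addition to Fisher or chi-squared, and it cannot analyse a day count. Finally, a count with many zeros would probably go to the Mann-Whitney test, which is less affected than the t test. Entry criteria that exclude short life expectancy, FEV1 below 50% and active cancer should also limit deaths.

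**Conclusion.** The concern holds in a limited form. As written, capture of antidepressant use depends on attendance, and the raw count takes no account of time alive and observed. If retention or survival differs by arm, the comparison is distorted: by undercounting if truncated counts are used, by selection if lost participants are set to missing.

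The size is modest unless retention differs a lot. Under the stated assumptions, a 10-point gap lowers mean days in the worse-retained arm by about 5 to 6% and hardly moves the error rate. A 20-point gap lowers them by about 12%, with false-positive rates of roughly 7 to 18% depending on test and level of use. The effect of death is certain in mechanism but not sized here, because the documents give no mortality figures.

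The documents do not support saying that participants who leave are counted as low users, or that an arm difference will arise. The point concerns long-term sub-study endpoints only.

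**What to change.** 1. **Source.** State that antidepressant prescriptions to month 36 are retrieved from the patient record for every randomised participant, whether or not visits are attended, unless consent to data use is withdrawn. First confirm that the accessible record shows the prescriptions the endpoint needs; the article does not say so.
2. **Day count.** Define the endpoint as treated days per day alive and observed, or fit a count model with log observed time as offset. Observation ends at death, withdrawal of data consent or month 36. Report deaths and observed time by arm beside it, because a rate while alive answers a different question from total days.
3. **New starts.** Make the already planned time-to-event (Cox) analysis the main comparison over the same window, in place of Fisher or chi-squared.

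The cost is a record look-up for each participant who missed visits and a few lines of endpoint and analysis wording. No extra visits or participants are needed, and the primary endpoint and the sample size of 532 (600 recruited) are unchanged.

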### Analyses

Data will be analyzed (blinded) using intention-to-treat (ITT) principles, including all the data available, regardless of whether the intervention was completed or not. The aims of the ITT analysis are also to provide unbiased comparisons among the two study groups and to avoid the effects of potential study dropouts and protocol deviations. Patients in the intervention group will be compared to patients in the control group.

For the primary outcome, the percentage of patients who have ceased smoking in each group will be calculated and the two groups will be compared using logistic regression. For the dichotomous outcomes and the nominal outcomes, both presented as counts and percentages, Fisher’s exact test and chi-squared test will be used, and the timed dichotomous outcomes will be visualized through Kaplan-Meier plots. In addition, the ordinal outcomes (also presented as counts and percentages) will be analyzed with the Mann-Whitney *U* test. Continuous outcomes will be expressed as means, standard deviations, and interquartile ranges and will be analyzed with *t* tests if normally distributed and Mann-Whitney *U* tests if non-normally distributed. Furthermore, adjusted analyses will be performed with a multivariable Cox proportional hazards model, adjusting for baseline variables and calculating hazard ratio. In addition, the combined outcomes “number of admissions for exacerbations of COPD or death …” and “number of admissions for all causes or death …” will be analyzed in a generalized linear model. Data will be processed and analyzed in SAS with graphs generated therein and in other graph programs such as SPSS.

A Data Safety Monitoring Board, independent from sponsor and competing interests, will monitor the safety of the trial by conducting interim analyzes based on primary and secondary endpoints when half of the study population has completed the study, and thus recommend continuation or termination of the trial.

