## Abstract

**Background:**

Cigarette smoking is the leading cause of chronic obstructive pulmonary disease (COPD), and it contributes to the development of many other serious diseases. Smoking cessation in COPD patients is known to improve survival and reduce the number of hospitalization-requiring acute exacerbations of COPD. However, smoking cessation interventions in these patients have only been successful for approximately 15–20% for consistent smoking abstinence in 12 months. Thus, more effective interventions are needed for this patient group. The aim of this study is to determine whether a high-intensity intervention compared to a low-intensity intervention can increase the proportion of persistent (> 12 months) anamnestic and biochemical smoking cessation in active smokers with COPD.

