#### Secondary endpoints

Number of admissions for exacerbations of COPD or death within 12 months (continuous)Number of admissions for all causes or death within 12 months (continuous)Number of cardiovascular events^1^ within 12 months (continuous)Changes in CAT score from baseline over 12 months (categorical)Changes in FEV_1_ from baseline over 12 months (continuous)Changes in BMI^2^ from baseline over 12 months (continuous)Clinically relevant changes in HADS score from baseline over 12 months (categorical, change in category 0–7, 8–10, and 11–21 points)Occurrence of DNA from the following: *M. catarrhalis*, *H. influenzae*, and *P. aeruginosa* over 12 months^3^ (dichotomous, measured as change in test result from baseline)Changes in the total lung microbiome over 12 months^3^ (continuous, measured as change in the total composition of lung microbiome from baseline)Occurrence of smoking-related cancer^4^ within 12 months (dichotomous)Number of admissions requiring NIV treatment or admissions to intensive care or death within 12 months (continuous)Changes in status from MRC dyspnea score from < 3 to ≥ 3, over 12 months (dichotomous)

^1^Defined as cardiovascular death, acute myocardial infarction, or unstable angina pectoris [19].

^2^BMI loss more than 1 unit.

^3^These endpoints are only examined on the first 50 who stop smoking from the “high-intensity” group against the first 50 who do not stop smoking from the “low-intensity” group.

^4^Lung cancer, urothelial cancer, pancreatic cancer, esophageal cancer, pharyngeal cancer, laryngeal cancer, tongue cancer, oral cancer, and tonsil cancer.

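### Non-fatal timed outcomes are to be drawn as Kaplan-Meier curves, which by default censor deaths, so the plotted 36-month depression curves will lie slightly above the proportion of participants affected

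*Protocol article*

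**What the plan says.** Three statements in the Analyses section of the protocol article bear on this.

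- Summary and test: "For the dichotomous outcomes and the nominal outcomes, both presented as counts and percentages", and for these "Fisher’s exact test and chi-squared test will be used".
- Display: "the timed dichotomous outcomes will be visualized through Kaplan-Meier plots".
- Model: "adjusted analyses will be performed with a multivariable Cox proportional hazards model, adjusting for baseline variables and calculating hazard ratio". The outcomes that this model covers are not named.

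The endpoint lists show where the display instruction falls. Under Secondary endpoints there is "Occurrence of smoking-related cancer^4^ within 12 months (dichotomous"). Under Long-term (follow-up) endpoints there are occurrence of depression within 36 months, "Admission to psychiatry with depression as the primary diagnosis (dichotomous"), and new antidepressant treatment after baseline. The layout also allows the last two to be read as components of the depression outcome. No definition among these includes death. The endpoints that do include death (admissions or death) are typed as continuous. Survival at 12, 24 and 48 months is announced under Design but is not in the endpoint lists.

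The change in MRC dyspnea status is also typed dichotomous, but it is a score change without a natural event date. Whether it counts as timed is not said.

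**The concern.** Kaplan-Meier suits an outcome that nothing but end of observation can prevent from being seen. Death is different: a participant who dies without depression can no longer become depressed. The usual Kaplan-Meier calculation removes that person from the risk set as if the event could still come later. One minus Kaplan-Meier then estimates incidence in a population without deaths, which is at least as large as the share of randomised participants who are affected.

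The same outcome will also appear as a crude percentage. If follow-up is otherwise complete, that percentage equals the cumulative incidence, so the figure will sit above the table. The protocol's own premise is that "Smoking cessation in COPD patients is known to improve survival", so mortality could differ between the arms, and the excess with it. What is at stake is whether the figures of the 36-month depression sub-study agree with the percentages beside them. The primary endpoint and the sample size are not involved.

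**Working it through.** **Plan's own figure.** The documents state no incidence or mortality for these outcomes, so there is nothing on this point to reproduce. The only design figure, 532 (266 + 266), belongs to the primary endpoint. It reproduces with 10% v 20%, two-sided 5% and 90% power, and plays no part below.

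**Inputs.** From the protocol: horizons of 12 and 36 months, and cessation of 10% v 20% (Sample size section). Assumed, because not given: constant and independent hazards, event hazard h = 3.5–10% per year and death hazard d = 1–5% per year (36-month mortality 3–14%).

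**Formulas**, with T in years:

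- One minus Kaplan-Meier, deaths censored: 1 − exp(−hT)
- Cumulative incidence with death competing: h/(h+d) × [1 − exp(−(h+d)T)]

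**36 months (T = 3)**

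| h | d | 1 − KM | Cumulative incidence | Excess (points) |
|---|---|---|---|---|
| 0.035 | 0.01 | 0.0997 | 0.0982 | 0.15 |
| 0.07 | 0.03 | 0.1894 | 0.1814 | 0.80 |
| 0.07 | 0.05 | 0.1894 | 0.1764 | 1.3 |
| 0.10 | 0.05 | 0.2592 | 0.2416 | 1.8 |

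Second row written out: 1 − exp(−0.21) = 0.1894; 0.7 × [1 − exp(−0.30)] = 0.1814. Over the whole range the relative excess is about 1.4% to 7.5%. A wider grid (1 − KM of 5–30%, 36-month deaths of 3–15%) gives 0.07 to 2.2 points.

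**12 months (T = 1).** With 1 − KM of 1–5% and deaths of 1–5%, the excess runs from less than 0.01 to 0.12 points. At the upper end h = d = −ln 0.95 = 0.0513, so the cumulative incidence is 0.5 × (1 − 0.95²) = 0.0488 against 0.05. For the 12-month cancer outcome this is negligible.

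**Difference between arms.** Assume equal event hazards and a death hazard halved in quitters from day 1. The Kaplan-Meier curves are then equal in the two arms. Cumulative incidence differs by (quitter value − smoker value) × (0.20 − 0.10).

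- h = 0.035, d = 0.01 v 0.005: (0.0989 − 0.0982) × 0.10, about 0.01 point
- h = 0.07, d = 0.03 v 0.015: (0.1854 − 0.1814) × 0.10, or 0.04 point
- h = 0.10, d = 0.05 v 0.025: (0.2502 − 0.2416) × 0.10, or 0.09 point

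With about 300 per arm, one participant is 0.33 point, so this cannot be seen.

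**The case against.** The strongest reply is that little is at stake. The quantity to be reported is the crude percentage. With complete follow-up it already equals the cumulative incidence, and Fisher's exact and chi-squared tests compare exactly that. Kaplan-Meier is named only as a visual aid. The exclusion of FEV₁ below 50%, recent admission for exacerbation, active cancer and short life expectancy should keep mortality low. How death is handled in secondary figures is also often left to a fuller document. Most of this stands, and it sets the size of the point. It does not remove it: the article does name the display method, and that method is the wrong one for non-fatal events.

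Four stronger readings are tempting, and the document does not support them.

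- *These outcomes are tested only as crude counts.* The same section plans a Cox model, which uses event times. It leaves open which outcomes the model covers, but a time-to-event analysis is planned.
- *The reported incidence is inflated.* Only the plotted curve is.
- *The comparison of the arms is materially biased.* Under the assumptions above the distortion is below 0.1 point.
- *The protocol states that deaths are censored.* It does not say how deaths are handled. Censoring is inferred from the standard method.

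Nor does it follow that Fisher's exact and chi-squared tests must be replaced. That is a debatable choice, and the correction does not need it.

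**Conclusion.** The point holds as a minor one. The stated display does not suit the non-fatal timed outcomes in the endpoint lists. If deaths are censored in the usual way, the 36-month curves overstate the proportion affected by about 0.15 to 1.8 points; the 12-month cancer curve is practically unaffected. These sizes rest on assumed constant, independent hazards and on death rates that the document does not give. With mortality at the low end, which the exclusions make plausible, the excess is a few tenths of a point. Counts, percentages, their tests and the primary analysis are untouched.

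**What to change.** In the Analyses section, restrict Kaplan-Meier to survival. For the non-fatal timed outcomes, chiefly the 36-month depression outcomes, plot Aalen-Johansen cumulative incidence by arm with death as a competing event, and give the arm difference at the horizon with its 95% CI. Keep the planned Cox model and label its result for these outcomes a cause-specific hazard ratio. If a p-value is attached to the curves, use Gray's test: a log-rank test with deaths censored compares cause-specific hazards, not the cumulative incidences drawn. Fisher's exact and chi-squared tests for the percentages can stay.

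The cost is a change of wording. Deaths are already to be obtained from the Cause of Death Register and admissions from records (Data collection), and SAS, the planned software, has standard procedures for these curves. The plotted incidences become slightly lower. Where participants are lost for reasons other than death, curve and crude percentage can still differ, and a footnote to the figure should say so.

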### Sample size (statistical power calculation)

Type 1 error limit (*α*) of 5%. Power (1-*β*) of 90%.

The maximum smoking cessation rate for the “low-intensity group” is expected to be 10% in 12 months. With the above-described person-adapted, multi-component, intensive smoking cessation intervention in the “high-intensity group”, ≥ 20% of participants are expected to cease tobacco smoking for at least 12 months. Thus, a 10% absolute improvement in the likelihood of smoking cessation is expected, in this case, equivalent to the relative risk of smoking cessation on 2.0. This gives a sample size of 532 (266 + 266) persons. To account for possible withdrawal from the study and lost to follow-up, 600 participants will be recruited for the project.

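### Changes in FEV1 and BMI are tested without baseline as a covariate, which loses precision, and the BMI and HAM-D endpoints need a single, complete definition

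*Protocol article*

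**What the plan says.** All references are to the protocol article.

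- **Tests (Analyses).** "Continuous outcomes will be expressed as means, standard deviations, and interquartile ranges and will be analyzed with" a t test where the data look normal and a Mann-Whitney U test where they do not. Ordinal outcomes get Mann-Whitney. Dichotomous and nominal outcomes get Fisher's exact or chi-squared tests. The adjusted analyses are a multivariable Cox model giving a hazard ratio. A generalized linear model is named only for two admissions-or-death composites.
- **FEV1 and BMI (Secondary endpoints).** Both are changes from baseline over 12 months, marked continuous. Footnote 2, attached to BMI, reads "BMI loss more than 1 unit". FEV1 change to 36 months is also a long-term endpoint.
- **CAT (Secondary endpoints).** Change "in CAT score from baseline over 12 months" is marked categorical, and no categories are listed.
- **HAM-D (Long-term endpoints).** The endpoint is a "change in category 13–17, 18–24, and 25–52 points", over 36 months. HADS, by contrast, has classes 0–7, 8–10 and 11–21.
- **Data collection.** Spirometry is done at inclusion and at 3, 6, 12, 24 and 36 months. Weight is measured at inclusion and at 6, 12, 24 and 36 months. HAM-D is scored at inclusion and at 12, 24 and 36 months.

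**The concern.** Three things are at stake, none of them touching the primary endpoint.

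First, comparing raw changes between arms is less efficient than comparing follow-up values with baseline as a covariate, and every baseline value needed is already collected. Choosing between a t test and a rank test from the look of the data also leaves open which quantity is being compared until the data are in.

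Second, the BMI label and its footnote describe different endpoints. Under the Analyses section they lead to different tests, so two analysts could both follow the protocol and report different results.

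Third, sub-study 1 concerns depression over 36 months, and the Questionnaires section says HAM-D is there to suggest a risk of developing depression. A move from below 13 to 13 or above is then a transition of obvious interest, yet the listed categories do not classify it.

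**Working it through.** **The plan's own figure.** The only sample size calculation is for the primary endpoint. The low-intensity rate "is expected to be 10% in 12 months", the high-intensity rate is 20%, alpha is 5% and power is 90%. With pooled variance, two sides and no continuity correction:

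n per arm = [1.960 × √(2 × 0.15 × 0.85) + 1.282 × √(0.10 × 0.90 + 0.20 × 0.80)]² / 0.10² = 266 after rounding up, or 532 in total.

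This matches the article. It is used below only to supply 266 per arm; no power is claimed for any secondary endpoint.

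**Cost of leaving baseline out as a covariate.** Let s² be the variance at baseline and at follow-up (assumed equal) and r the correlation between them (assumed; the article gives none).

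- Variance of a change score: 2(1 − r)s²
- Residual variance after baseline adjustment: (1 − r²)s²
- Ratio: (1 − r²) / [2(1 − r)] = (1 + r)/2

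For power, set the effect so that the change-score test has 80% with 266 per arm. The standardised effect is then 1.960 + 0.842 = 2.802. Adjusted power is Φ(2.802/√ratio − 1.960).

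| Assumed r | Variance ratio | Variance reduction | Power with baseline covariate |
|---|---|---|---|
| 0.5 | 0.75 | 25% | 89.9% |
| 0.7 | 0.85 | 15% | 86.0% |
| 0.9 | 0.95 | 5% | 82.0% |
| 0.95 | 0.975 | 2.5% | 81.0% |

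**Does the named adjusted model help?** No. A Cox model needs a time to an event and returns a hazard ratio. A change in FEV1 or BMI at a scheduled visit is a measurement.

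**BMI: label against footnote.**

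| Reading | Test under the Analyses section | What a gain, or a loss of up to 1 unit, contributes |
|---|---|---|
| Continuous | t test or Mann-Whitney | its actual value |
| Loss of more than 1 unit | Fisher or chi-squared | the same as no change |

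If the footnote governs, and the change is normally distributed (assumption), a binary cut with event share p keeps φ(c)²/[p(1 − p)] of the information, where c is the cut-point. That is 64% at p = 50%, 49% at 20%, 34% at 10% and 22% at 5%. The event share is not given. The Interventions section has the dietician address weight in both directions, which fits the continuous reading better.

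**HAM-D: which moves are classified.** The scale is taken to start at 0; the article gives its top as 52.

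| Move between visits | Classified as written? |
|---|---|
| Between 13–17, 18–24 and 25–52 | yes |
| From below 13 to 13 or above | no |
| From 13 or above to below 13 | no |
| Remains below 13 | no |

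**The case against.** The strongest reply is that a condensed article need not list covariates and that a t test on change is a legitimate analysis. Part of this stands. Baseline does enter by subtraction, randomisation makes the comparison valid, and the gain from adjustment may be small for a stable measure. But the article is not merely silent: it fixes the tests, makes the choice depend on normality, and names as its adjusted analysis a model that does not fit these endpoints.

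For HAM-D, an unlisted class below 13 may well be intended. That is a fair guess, but it is not written, and HADS shows that the authors listed a scheme starting at 0 elsewhere.

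Several stronger readings are tempting and are not supported:

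- **The tests are biased.** They are not; the loss is precision.
- **Many participants cannot register a change.** The article gives no baseline distribution of MRC or HAM-D, so no share can be claimed. For BMI the statement is false: under the footnote anyone can still register a loss.
- **The MRC endpoint is wrong.** "Changes in status from MRC dyspnea score from" below 3 to 3 or more counts worsening across a stated threshold. It ignores improvement and those already at 3 or above, but it is a defined choice, not an error.
- **The depression sub-study fails.** HADS, psychiatric admissions, new antidepressant treatment and days on treatment also feed it. Only the HAM-D component is incomplete.
- **Calling CAT categorical is a fault of substance.** It is only a label, and no consequence specific to CAT can be shown.

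It is also fair to say that changing endpoint wording in a registered, open-label trial carries an amendment and transparency cost.

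**Conclusion.** The point holds as an improvement to the analysis plus two corrections of definition. For FEV1 and BMI, the planned tests are valid but give up 2.5% to 25% of the variance for assumed correlations from 0.95 down to 0.5. That is 1 to 10 percentage points of power from an 80% base with 266 per arm. These figures rest on equal variances and on correlations the article does not supply; at high correlation the gain is small.

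The BMI label and footnote contradict each other, and the HAM-D categories are incomplete below 13. Both follow directly from the text; the only assumption is that HAM-D starts at 0. The changes are worth making, but nothing here affects the primary endpoint, the 532 required or the 600 to be recruited.

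**What to change.** 1. **FEV1 and BMI.** Analyse by ANCOVA, or by a mixed model over the scheduled visits, with baseline value, arm and the two stratification factors (age > 65 vs. ≤ 65; > 10 vs. ≤ 10 cigarettes a day). Treat CAT the same way if it is kept as a numeric score. Apply the same approach to FEV1 at 36 months.
2. **Choice of test.** Drop the normality-based switch and name one analysis per endpoint in advance.
3. **BMI.** Define it once, as continuous change in both directions. Keep loss of more than 1 unit, if wanted, as a separate descriptive item.
4. **HAM-D.** Add a 0–12 class, or analyse the score with baseline as covariate, so that moves into and out of 13 and above are classified.
5. **MRC (optional).** Keep the stated endpoint. An ordinal, baseline-adjusted analysis may be added as supportive.

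The cost is wording and some programming; no new data or visits are needed. Items 3 and 4 change the text of published endpoints, so they need a dated amendment and, where the registry entry carries the same wording, an update there, both made before outcome data are compared by arm.
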